## Abstract

**Background:**

Postoperative pulmonary complications (PPCs) are the most common perioperative complications following surgical site infection (SSI). They prolong the hospital stay and increase health care costs. A lung-protective ventilation strategy is considered better practice in abdominal surgery to prevent PPCs. However, the role of the inspiratory oxygen fraction (FiO_2_) in the strategy remains disputed. Previous trials have focused on reducing SSI by increasing the inhaled oxygen concentration but higher FiO_2_ (80%) was found to be associated with a greater incidence of atelectasis and mortality in recent research. The trial aims at evaluating the effect of different FiO_2_ added to the lung-protective ventilation strategy on the incidence of PPCs during general anesthesia for abdominal surgery.

**Methods and design:**

PROtective Ventilation with a low versus high Inspiratory Oxygen fraction trial (PROVIO) is a single-center, prospective, randomized controlled trial planning to recruit 252 patients undergoing abdominal surgery lasting for at least 2 h. The patients will be randomly assigned to (1) a low-FiO_2_ (30% FiO_2_) group and (2) a high-FiO_2_ (80% FiO_2_) group in the lung-protective ventilation strategy. The primary outcome of the study is the occurrence of PPCs within the postoperative 7 days. Secondary outcomes include the severity grade of PPCs, the occurrence of postoperative extrapulmonary complications and all-cause mortality within the postoperative 7 and 30 days.

**Discussion:**

The PROVIO trial assesses the effect of low versus high FiO_2_ added to a lung-protective ventilation strategy on PPCs for abdominal surgery patients and the results should provide practical approaches to intraoperative oxygen management.

**Trial registration:**

www.ChiCTR.org.cn, identifier: ChiCTR18 00014901. Registered on 13 February 2018.

**Electronic supplementary material:**

The online version of this article (10.1186/s13063-019-3668-x) contains supplementary material, which is available to authorized users.

## Background

About 2.0 to 5.6% of more than 234 million patients undergoing surgery develop postoperative pulmonary complications (PPCs), especially after general and vascular surgeries (approximately 40%), which makes PPCs the most common perioperative complications following surgical site infection (SSI) [1–6]. PPCs, especially respiratory failure, add to the morbidity and mortality risk in hospitalized patients [1, 4, 5]. Moreover, PPCs prolong hospital stay and increase medical expense and resource utilization [2, 5]. A reduction of PPCs is a very important evaluation index of medical quality management. A possible explanation for increasing morbidity in patients who develop PPCs is that mechanical ventilation under general anesthesia results in gas-exchange impairment, a local inflammatory response and circulatory disorder [7, 8]. Thus, decreased lung volumes, ventilator-induced lung injury and atelectasis are strongly associated with the incidence of PPCs [9].

Prior studies noted that so-called lung-protective ventilation, referring to low-tidal-volume (V_T_), appropriate positive end-expiratory pressure (PEEP) level and recruitment maneuvers, seems to be the optimum option for the surgical and intensive care unit (ICU) populations [10–13]. The decrease in PPCs, mortality and health care costs have been observed in the protective-ventilated population. On the basis of the robust evidence available, a combination of low V_T_ (6–8 ml/kg of predicted body weight) [11, 14], a level of PEEP at 5–8 cmH_2_O [15] and repeated recruitment maneuvers [16] are now widely adopted.

Setting the inspiratory oxygen fraction (FiO_2_) intraoperatively is a significant task of anesthetists, but has not been based on evidence-based guidelines. Obtaining comprehensive knowledge about hyperoxia caused by high FiO_2_ has been stressed as important by clinicians over the past few decades, including its potentially deleterious effects on lung. Even mildly elevated FiO_2_ levels have been reported to exacerbate lung injury by up-regulating pro-inflammatory cytokines and inducing neutrophil infiltration in the alveolar spaces [17–19].

Even if there is no significant difference in pulse oximetry and the oxygenation index for several time-points with 30 or 80% FiO_2_ intraoperatively, hyperoxia and substantial oxygen exposure are common in clinical practice [20, 21]. Questions have been raised about the use of oxygen in ventilated patients undergoing elective surgery. A recent systematic review revealed that the trials of this decade about the effects of FiO_2_ on SSI have been inconclusive, and we should also focus on clinically relevant pulmonary side-effects and other adverse events (AEs) [22–25]. In addition, exposure to oxygen is related to adverse effects in critically ill patients [26, 27]. The ideal FiO_2_ level in the lung-protective ventilation strategy to protect against PPCs and improve clinical outcomes has not been addressed in the perioperative period.

The relationship between FiO_2_ and PPCs in surgical patients is mainly affected by a hyperoxia-induced change in the respiratory mechanism. Higher FiO_2_ seems to be associated with pulmonary complications and adverse clinical outcomes, but the existing evidence is insufficient to warrant its effect to promote PPCs [28–30]. We hypothesize that a low level of FiO_2_ (30%) compared with high FiO_2_ (80%) could decrease the incidence of PPCs in patients undergoing abdominal surgery when lung-protective ventilation strategy is administered.

## Methods and design

### Study design

The PROVIO trial is a single-center, prospective, randomized controlled and two-arm study and is conducted in accordance with the Declaration of Helsinki. The trial will be conducted in West China Hospital of Sichuan University, China. We aim to assess the effect of FiO_2_ in a lung-protective ventilation strategy, in an abdominal surgical population of patients, on PPCs, extrapulmonary complications (e.g., SSI, sepsis, etc.), hospital stay and mortality.

The protocol follows the Standard Protocol Items: Recommendations for Interventional Trials (SPIRIT) 2013 Statement. The SPIRIT checklist can be found inAdditional file 1. The diagram of the Consolidated Standards of Reporting Trials (CONSORT), which are also followed, is presented in Fig. 1.

**Fig. 1 Fig1:**
[figure not shown]
Consolidated Standards of Reporting Trials (CONSORT) diagram of the PROVIO trial

### Study population

The inclusion criteria of the study are: American Society of Anesthesiologists (ASA) physical status I–III patients aged 18 years or older, scheduled for elective abdominal surgery with an expected duration of at least 2 h and planned to be extubated in the operating room. Laparotomy and laparoscopy surgery will not be restricted. Patients are ineligible if they have suffered from pneumothorax, acute lung injury or acute respiratory distress syndrome within the last 3 months. Other exclusion criteria are: a diagnosis of heart failure (New York Heart Association classes; NYHA IV), chronic renal failure (glomerular filtration rate < 30 ml/min), serious hepatic diseases (e.g., hepatic failure), scheduled for reoperation or postoperative mechanical circulatory support, known pregnancy, participation in another interventional study, and with a body mass index (BMI) of > 30 kg/m^2^.

### Randomization, blinding and bias minimization

Patients will be recruited from West China Hospital of Sichuan University. Consecutive male or female patients aged 18 years or older who will undergo abdominal surgery under general anesthesia are screened for study eligibility. Randomization will be performed using a computer-generated randomization list (SPSS 22.0) with an allocation rate of 1:1. The allocation is concealed in an opaque envelope and will be sent to the attending anesthetist by a blinded investigator.

Given the characteristics of the study, the attending anesthetist must know the intervention. Researchers, including the investigator in the operating room, the data collector and the data analyzer, will all be blinded to the randomization arm. All the surgeons, nurses and anesthetists in the post-anesthesia care unit (PACU) will not know the allocation. Postoperative visits and outcome assessment will be performed by a blinded investigator. Emergency unblinding is permissible if hypoxemia occurs (defined as pulse oxygen saturation (SpO_2_) < 92% or partial pressure of oxygen in arterial blood (PaO_2_) < 60 mmHg).

### Standard procedures

The risk of PPCs will be assessed using the Assess Respiratory Risk in Surgical Patients in Catalonia (ARISCAT) risk score [31] before randomization (Table 1). An investigator assesses the individual risk of PPCs with the seven predictors of the ARISCAT risk score (age, SpO_2_, respiratory infection in the last month, preoperative anemia, duration of surgery, and whether an emergency procedure). The ARISCAT score will help to analyze the effect of FiO_2_ to intermediate-high-risk patients who obtain a score of more than 26. All patients receiving an assessment will be included and randomized.

**Table 1 Tab1:** Assess Respiratory Risk in Surgical Patients in Catalonia (ARISCAT) risk score in the logistic regression model

	βcoefficient	Score *
Age (years)		
≤ 50	0	0
51–80	0.331	3
> 80	1.619	16
Preoperative SpO_2_ (%)		
≥ 96	0	0
91–95	0.802	8
≤ 90	2.375	24
Respiratory infection in the last month		
No	0	0
Yes	1.698	17
Preoperative anemia (Hb ≤10 g/dl)		
No	0	0
Yes	1.105	11
Surgical incision		
Peripheral	1.480	15
Upper abdominal	2.431	24
Intrathoracic		
Duration of surgery (h)		
≤ 2	1.593	0
2–3	2.268	16
> 3	0.768	23
Emergency procedure		
No	0	0
Yes	0.768	8

*A risk score ≥ 26 predicts an intermediate to high risk for postoperative pulmonary complications after abdominal surgery. The simplified risk score was the sum of each logistic regression coefficient multiplied by 10, after rounding off its value

*Hb* hemoglobin

All randomized participants will receive standard care and monitoring including a five-lead electrocardiogram, SpO_2_, blood pressure (invasive or noninvasive) and end-tidal carbon dioxide (E_T_CO_2_). The attending anesthetist responsible for the patient can choose the bispectral index (BIS), muscle-relaxant monitoring and cardiac-output monitoring techniques according to clinical routines.

There will be no restriction to the anesthetic regimen and individualized health care will be performed intraoperatively. Use of antiemetics and muscle-relaxant antagonists (mainly neostigmine) will be recorded in the case report form (CRF).

### Intraoperative ventilatory management

Pre-oxygenation will be prescribed for 5 min at 100% FiO_2_ using a mask. In accordance with the group allocation, the participants will be randomized to receive a low (30%) or a high (80%) FiO_2_ throughout the whole period of intraoperative mechanical ventilation after tracheal intubation. The FiO_2_ level is implemented through adjusting the air-oxygen ratio when the total gas flow remains at 2 L/min. The FiO_2_ in our protocol refers to the actual fraction of inspired oxygen presented in the display panel on the anesthesthetic machine. Table 2 shows the ventilation settings.

**Table 2 Tab2:** Intraoperative ventilation settings for the PROVIO trial

	Low-FiO_2_ group	High-FiO_2_ group
FiO_2_	0.30	0.80
V_T_	8 ml/kg	8 ml/kg
PEEP	6–8 cmH_2_O	6–8 cmH_2_O
I:E	1:2	1:2
RR	Adjusted according to E_T_CO_2_ (35–45 mmHg)	Adjusted according to E_T_CO_2_ (35–45 mmHg)
P_max_	30 cmH_2_O	30 cmH_2_O

*E*_*T*_*CO*_*2*_ end-tidal carbon dioxide, *FiO*_*2*_ inspiratory oxygen fraction, *I:R* Inspiratory to Expiratory ratio, *PEEP* positive end-expiratory pressure, *P*_*max*_ maximum peak airway pressure, *RR* respiratory rate, *V*_*T*_ tidal volume

Intraoperative ventilation in all participants will be performed via the lung-protective ventilation strategy. A recruitment maneuver with peak airway pressure (P_aw_) of 30 cmH_2_O for 30 s will be performed instantly after intubation, every 60 min after intubation and before extubation. Other settings are shown in Table 2. Ventilatory parameters, including tidal volume (V_T_), minute volume (MV), airway pressure (P_aw_), plateau pressure (P_plat_), fresh gas flow, PEEP and FiO_2_, will be monitored.

After extubation, patients will be sent to the PACU or the ward where they will be oxygenated with 2 L/min, pure oxygen via a nasal tube over 24 h. At the same time, they will receive standard monitoring.

### Intraoperative care

After induction, standard intraoperative care will be applied in both groups to reach a target of standard state (Table 3). Vasoactive drugs can be used in patients with unstable hemodynamics as appropriate.

**Table 3 Tab3:** Standard state target

	Parameter	Value
Hemodynamics	Mean arterial pressure (MAP)	70 mmHg < MAP < 100 mmHg
Hemodynamics	Heart rate (HR)	50/min < HR < 100/min
Oxygenation	Pulse oxygen saturation (SpO_2_)	≥ 92%

### Rescue strategies for intraoperative hypoxemia

Around 30% FiO_2_ has been proved to be safe in mechanically ventilated patients and rarely causes hypoxemia [21]. We designed a rescue strategy for patients in whom SpO_2_, measured by pulse oximetry, fell to less than 92% or PaO_2_ to less than 60 mmHg for more than 1 min.

Endotracheal-tube displacement, airway-secretion blockage, bronchospasm, pneumothorax, and hemodynamic change would all be checked for. After excluding these as underlying causes, a rescue recruitment maneuver with P_aw_ 30 cmH_2_O for 30 s will be implemented [12, 16, 32]. If this were to fail, FiO_2_ and ventilation settings would be altered until acquiring the required oxygenation (SpO_2_ ≥ 92% or PaO_2_ ≥ 60 mmHg).

### Outcome measurements

The primary outcome is the occurrence of pulmonary complications within the first 7 days postoperatively. The definition of PPCs follows the ARISCAT study (respiratory infection, respiratory failure, bronchospasm, atelectasis, pleural effusion, pneumothorax or aspiration pneumonitis.) [4].

The secondary outcomes include the occurrence of PPCs in the postoperative 30 days; SSI, postoperative nausea and vomiting (PONV) in the postoperative 7 days; the severity grade of pulmonary complications in the postoperative 7 and 30 days (Table 4); and death rate in the postoperative 7 and 30 days.

**Table 4 Tab4:** Grades of pulmonary complications

Postoperative pulmonary complication grade	
Grade 1	Cough, dry Microatelectasis: abnormal lung findings and temperature > 37.5 °C without other documented cause; normal chest radiograph Dyspnea, not due to other documented cause
Grade 2^a^	Cough, productive, not due to other documented cause Bronchospasm: new wheezing or preexistent wheezing resulting in a change in therapy Hypoxemia: SpO_2_ < 90 in room air Atelectasis: gross radiological confirmation (concordance of 2 independent experts) plus either temperature > 37.5 °C or abnormal lung findings Hypercarbia (PaCO_2_ > 50 mmHg), requiring treatment
Grade 3	Pleural effusion, resulting in thoracentesis Pneumonia: radiological evidence (concordance of 2 independent experts) plus clinical symptoms (two of the following: leukcocytosis or leukopenia, abnormal temperature, purulent secretions), plus either a pathological organism (by Gram stain or culture), or a required change in antibiotics Pneumothorax Noninvasive ventilation, strictly applied to those with all of the following: (a) SpO_2_ ≤ 92% under supplemental oxygen; (b) need of supplemental oxygen > 5 L/min; and (c) respiratory rate ≥ 30 bpm Reintubation postoperative or intubation, period of ventilator dependence does not exceed 48 h
Grade 4	Ventilatory failure: postoperative ventilator dependence exceeding 48 h, or reintubation with subsequent period of ventilator dependence exceeding 48 h
Grade 5	Death

^a^We only classified as grade 2 if two or more items in grade 2 were present

*PaCO*_*2*_ partial pressure of arterial carbon dioxide, *SpO*_2_ pulse oxygen saturation

Pulmonary complications will be scored with a grade scale ranging from 0 to 5 adapted from Kroenke et al., Hulzebos et al., Fernandez-Bustamante et al. and Canet et al. [4, 5, 33, 34]. Grade 0 in the scale represents no PPCs, grades 1–4 represent increasing severity levels of pulmonary complications, and grade 5 represents death before discharge. SSI will be defined with the criteria from the Centers for Disease Control and Prevention (CDC) [35].

Tertiary outcomes in the first 7 and 30 days postoperatively are as follows:
Sepsis: the infection-centric systemic response which needs to meet two or more criteria of the systemic inflammatory response syndrome (SIRS) [36]Septic shock: defined as a composite of sepsis-induced response, perfusion abnormalities, and hypotension despite adequate fluid resuscitation [36]Myocardial ischemia [37]Heart failure [37]Urinary system infection [37]

Acute kidney injury: defined according to the Kidney Disease Improving Global Outcomes (KDIGO) criteria [38]
6.Anastomotic fistula7.Reintubation8.Unplanned admission to the ICU9.Hospital length of stay postoperatively

### Data collection and follow-up

The study will be conducted in the operating room and visits are restricted during the screening, hospitalization and follow-up periods. The primary and secondary outcomes will be measured on postoperative days 1, 2, 3, 5 and 7 or at discharge by interview. On postoperative day 30, participants will be contacted by phone (Fig. 2). Demographic and baseline data will be collected preoperatively, which include age, sex, weight, BMI, ASA physical status, ARISCAT risk score, smoking status, pulmonary status (chronic pbstructive pulmonary disease (COPD), atelectasis, asthma respiratory infection within the last 3 months, use of ventilatory support), routine laboratory tests (hemoglobin, white blood cell count, platelet count, neutrophil count) and medical history.

**Fig. 2 Fig2:**
[figure not shown]
Standard Protocol Items: Recommendation for Interventional Trials (SPIRIT) schedule of enrollment, interventions and assessments

Both intraoperative surgery- and anesthesia-associated data will be recorded, including type of surgery, surgical incision or approach, duration of surgery and ventilation, blood loss, transfusion of blood products, fluid balance (calculated by subtracting the measurable fluid losses from measurable fluid intake during anesthesia), drugs during anesthesia (e.g., anesthetics and antiemetics), adjustment of ventilatory parameters or FiO_2_, hypoxemia events, the need for rescue strategy, number of emergency recruitment maneuvers, and unplanned admission to the ICU.

Postoperative visits will be conducted daily and clinical data required to assess PPC grade include body temperature, lung auscultation, symptoms (e.g., cough, expectoration and dyspnea), chest-imaging manifestations, and laboratory tests. Surgical incision assessment, PONV and other outcomes will also be measured and collected daily according to the evaluation criterion mentioned above.

The Data and Safety Monitoring Board (DSMB) composed of five independent individuals is set up to supervise the overall conduct of the study (the screening, recruitment and adherence to the protocol). The DSMB is responsible for checking and ensuring the completeness and validity of data recording. The interim analysis will be conducted when the first 120 participants are recruited and have been visited to completion. The DSMB has access to patient allocation, but the results of the interim analysis will be treated as strictly confidential.

### Study drop-out

Participants have the right to withdraw from the study at any time without any consequences for further treatment. Investigators have the right to terminate the study at any time in consideration of the best interests of the participants. Both situations will be recorded in the CRF and discussed.

Any AEs and treatment side-effects will be sent to the DSMB which will discussed whether the participant should drop out accordingly.

### Statistical considerations

The sample size required was estimated based on the investigative data in our medical center. The pilot study showed that PPCs (respiratory infection, respiratory failure, bronchospasm, atelectasis, pleural effusion, pneumothorax or aspiration pneumonitis) occurred in 50.4% patients received 80% FiO_2_ after abdominal surgery (sample size: 100). And assuming a round 50% rate of PPCs in the high-FiO_2_ (80%) group, we calculated that a total sample size of 252 patients (126 in each group) will have 80% power to detect a relative risk reduction of 35% in PPCs between groups, at a two-sided alpha level of 0.05 and 5% drop-out. We will conduct a sample size reassessment after recruiting half of the patients for safety consideration.

All statistics will be analyzed by SPSS 22.0 statistical software (IBM Corporation, Chicago, IL, USA) through the intention-to-treat principle, which covers all randomized patients receiving surgery. Participants with adjusted FiO_2_ values are still treated as the low-FiO_2_ population when analyzed. In a descriptive analysis of the population, mean and standard deviation (SD) will be used for normally distributed variables, medians and interquartile ranges used for non-normally distributed variables and percentages used for categorical variables. Stratified description will be used as appropriate.

There will be a baseline comparison of age, gender, BMI, type of surgery, surgical approach, duration of surgery and ARISCAT score between groups and logistic regression analysis will be performed if an imbalance between groups exists. The Student’s *t* test will be used for continuous, normally distributed variables and the Mann-Whitney *U* test will be used for continuous, non-normally distributed data. The primary and secondary outcomes will be compared using the *χ*^2^ test or Fisher’s exact test, while multiple logistic-regression analysis will be used to identify hazards. A two-sided *P* value < 0.05 is considered statistically significant.

A custom-made folder is made to store the participants’ data, which consists of documents and forms. Only blinded researchers have access to the folder. Only when the study is complete will the investigators obtain the data.

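### Covariate adjustment of the primary outcome hangs on a chance baseline imbalance, its standing against the named test is unclear, and ARISCAT is not a fixed covariate

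*Protocol article*

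**What the plan says.** All of the analysis text is in the protocol article, Statistical considerations.

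- **Screen:** "There will be a baseline comparison of age, gender, BMI, type of surgery, surgical approach, duration of surgery and ARISCAT score between groups".
- **Consequence of the screen:** "logistic regression analysis will be performed if an imbalance between groups exists". No criterion for imbalance and no list of entering covariates is given.
- **Primary test:** "The primary and secondary outcomes will be compared using the" chi-square or Fisher's exact test. This sentence carries no condition.
- **A further regression:** "multiple logistic-regression analysis will be used to identify hazards", without named covariates. It is not described as the analysis of the treatment effect.

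Two other places bear on the variables screened:

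- Data collection and follow-up, in the text after Fig. 2, files duration of surgery with the operative record: "Both intraoperative surgery- and anesthesia-associated data will be recorded, including type of surgery, surgical incision or approach, duration of surgery and ventilation".
- Standard procedures says "The risk of PPCs will be assessed using the Assess Respiratory Risk in Surgical Patients in Catalonia (ARISCAT) risk score", with the score taken "risk score [31] before randomization". The use named there is an analysis of intermediate-to-high-risk patients.

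**The concern.** Allocation is by a computer-generated 1:1 list, so any difference between arms in a true baseline variable is chance. A check for such differences says nothing about whether a covariate predicts the outcome, and that is what makes adjustment worthwhile. A rule that fits a model only when the check is positive has three consequences.

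1. Some trials end with two results for the primary outcome, on different scales (a comparison of proportions and an adjusted odds ratio), and the text does not rank them.
2. Actual duration of surgery arises after randomization, while the randomized oxygen fraction is being given. It does not belong in a baseline check that decides on adjustment.
3. A score built to predict pulmonary complications, available for everyone before allocation, has no assured place in the primary comparison.

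**Working it through.** **Plan's own figure.** Inputs from Statistical considerations: 50% in the high-FiO2 arm, 35% relative reduction (so 0.50 × 0.65 = 0.325), two-sided alpha 0.05, 80% power, 5% drop-out.

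n per arm = (1.96 + 0.8416)² × [0.5 × 0.5 + 0.325 × 0.675] / 0.175² = 7.849 × 0.4694 / 0.030625 = 120.3.

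120 × 1.05 = 126 per arm, or 252 in total. The stated size reproduces, and it was set for the unadjusted test. Power of that test by the pooled formula is 79.0% at 120 per arm and 80.9% at 126.

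**How often chance triggers the regression.** Assumption: imbalance means P<0.05, the only significance level in that section.

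- Seven independent comparisons: 1 - 0.95⁷ = 0.302.
- Four effectively independent comparisons: 1 - 0.95⁴ = 0.185. The lower figure is relevant because ARISCAT itself contains age, incision and duration.

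**What the rule does to error and power.** Simulation with 120 per arm and 6,000 trials per scenario: seven independent covariates, one of them prognostic. The event rate is 50% in both arms under the null and 50% vs 32.5% under the alternative. When the trigger fires, only the imbalanced covariates enter the model. The documents give no prognostic strength, so it is varied as an assumed odds ratio per SD.

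| Odds ratio per SD (logit SD) | 1.5 (0.41) | 2 (0.69) | 2.5 (0.92) | 3 (1.10) |
|---|---|---|---|---|
| Power, unadjusted | 79.7% | 79.3% | 79.2% | 79.5% |
| Power, triggered rule | 79.4% | 79.2% | 79.6% | 79.9% |
| Power, score always in model | 80.7% | 82.8% | 85.2% | 86.9% |
| Type I error, triggered rule | 4.3% | 4.3% | 4.2% | 4.4% |
| Type I error, better of unadjusted and triggered | 4.6% | 4.8% | 4.8% | 5.0% |
| Type I error, score always in model | 4.6% | 5.1% | 5.0% | 4.7% |

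The unadjusted and triggered results disagreed on significance in about 1% of null trials and about 2% under the alternative.

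Further runs up to logit SD 1.3 put always-adjusted power at about 89% and the better-of-two error at no more than about 5.5%. With 4,000 trials the simulation standard error at 5% is √(0.05 × 0.95 / 4000) = 0.34 points, so 5.5% is hardly distinguishable from nominal.

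If a triggered model took in the whole list, ARISCAT would enter each time. The rule would then recover roughly 30% of the gain, at most about 0.30 × 9 = 2.7 points.

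**The case against.** The strongest reply is that the plan already has a primary test. The chi-square or Fisher sentence is unconditional, the trial is sized for it, and the regression reads naturally as a supplement. That reading is fair, and a reader who infers that the primary analysis definitely switches to an adjusted one goes beyond the text. What stands is that the text leaves the relation between the two results open.

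A reader might also infer that choosing between two P values inflates the type I error. Simulations do give 6.1-7.2% if success is claimed on either the unadjusted test or an adjusted test fitted in **every** trial (logit SD 0.7-1.3). The protocol fits the adjusted model only after an imbalance, and under that rule the inflation all but disappears. The regression meant to identify hazards is unconditional, but nothing says it will be used to claim a treatment effect.

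Nor is ARISCAT idle unless imbalanced. It has its own stated use in the higher-risk patients and could enter the hazards model. It is simply not prespecified for the primary comparison.

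On duration, the list does not say actual duration, and expected duration is an eligibility criterion. The only place where duration of surgery is recorded as data is the operative record, however, so the listed variable needs clarifying. No bias from it has been quantified.

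Finally, an imbalance threshold and a covariate list may properly be left to an analysis plan. Their absence is not the finding. The finding is that the article itself fixes a data-dependent trigger, which an analysis plan that follows it would inherit.

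**Conclusion.** The point holds as a defect of specification and efficiency. The stated rule leaves the standing of an adjusted result undefined in the trials where it fires, about 19-30% by chance alone if imbalance means P<0.05. It also earns essentially none of the power that a fixed prognostic covariate offers: 79-80% under the rule against about 81-89% with prespecified adjustment, a gain of about 1 to 9 points over an assumed logit SD of 0.4-1.3. At the weak end the gain is negligible, and the documents do not show where ARISCAT would fall in this population. The documents do not support a claim of inflated type I error: it stays at about 5% or below under the rule, and at most about 5.5% if the better result is picked.

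**What to change.** Before unblinding, prespecify one primary analysis: logistic regression of 7-day pulmonary complications on arm and the pre-randomization ARISCAT score, scored with expected duration of surgery, whatever the baseline table shows. Report a standardised risk difference and risk ratio with 95% confidence intervals, and keep the unadjusted chi-square or Fisher test as supportive. Delete the imbalance trigger. Keep actual duration of surgery descriptive and out of any model for the treatment effect.

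The cost is a change of wording and one regression on data already collected. The sample size of 252 need not change. The small downside is the standardisation step needed to turn the model into a risk difference and risk ratio.

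### The ordered 0–5 severity grade is assigned a chi-square or Fisher test, which ignores order; an ordinal method should be named for it

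*Protocol article*

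**What the plan says.** All references are to the protocol article.

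- **The outcome.** Outcome measurements lists among the secondary outcomes "the severity grade of pulmonary complications in the postoperative 7 and 30 days (Table 4"). The same section says: "Pulmonary complications will be scored with a grade scale ranging from 0 to 5".
- **The scale is ordered.** Grade 0 means no complication; above it, "grades 1–4 represent increasing severity levels of pulmonary complications, and grade 5 represents death before discharge".
- **The test.** Statistical considerations states: "The primary and secondary outcomes will be compared using the *χ*^2^ test or Fisher’s exact test".
- **The rank test.** The same paragraph names Mann-Whitney U, but the "test will be used for continuous, non-normally distributed data".
- **Other methods named.** Logistic regression is planned for baseline imbalance and for identifying risk factors. No trend test, ordinal model or cut-point is named for the grade.
- **Planning figures.** The sample size rests on "assuming a round 50% rate of PPCs in the high-FiO_2_ (80%) group" and "80% power to detect a relative risk reduction of 35% in PPCs between groups", "at a two-sided alpha level of 0.05 and 5% drop-out". These describe the binary primary outcome. The article gives no expected distribution, effect size or power for the grade.

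**The concern.** The article states a choice of test, so this is not a detail left open, and the choice does not fit the scale it is applied to.

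If the grade labels are permuted, the Pearson chi-square and the Fisher test on a 2×6 table return the same p-value. Moving patients from grade 4 to grade 1 counts no differently from any other rearrangement of the same size. The trial's hypothesis is directional: low FiO2 should reduce complications. The natural question for the grade is therefore whether the distribution shifts towards milder levels. A 5-degree-of-freedom test asks only whether the two patterns differ in any way, and it yields no single effect measure.

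At stake is the reading of one secondary outcome at two time points. A real, consistent shift in severity could be missed, and a significant result would need the raw percentages to show what it means.

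**Working it through.** **1. The plan's own figure.** High-FiO2 rate 0.50; a 35% relative reduction gives 0.50 × 0.65 = 0.325. With unpooled variance:

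n = (1.96 + 0.8416)² × [0.5 × 0.5 + 0.325 × 0.675] / 0.175² = 7.849 × 0.4694 / 0.030625 = 120.3 per arm.

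Allowing for 5% drop-out gives 120.3 / 0.95 = 126.6, or 120.3 × 1.05 = 126.3. Both agree with the stated 126 per arm. The sample size reproduces and is not in question.

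**2. Inputs for the grade.** Analysed per arm: 126 × 0.95 = 119.7, taken as 119. Odds ratio for grade 0: (0.675 / 0.325) / (0.50 / 0.50) = 2.077. The grade distributions are assumptions. Example A has 50/20/15/10/3/2% in grades 0–5 of the high-FiO2 arm. Applying 2.077 to every cumulative odds gives 67.5/15.4/9.3/5.4/1.5/1.0% in the low-FiO2 arm.

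**3. Simulated power** (20,000 trials per scenario, two-sided 0.05, 119 per arm, tie-corrected Mann-Whitney):

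| Effect | Grades occupied | Chi-square | Mann-Whitney | Loss (points) |
|---|---|---|---|---|
| Proportional odds, OR 2.077, four assumed distributions | 6 | 56–59% | 81–82% | 23–25 |
| Every grade 1–5 multiplied by 0.65, same distributions | 6 | 52–56% | 75–76% | 20–23 |
| Both effects, 50/42/6/2% | 4 | 63–64% | 77–80% | 14–16 |
| Both effects, 50/30/20% | 3 | 69–73% | 76–81% | 6–9 |

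**4. Analytic check.** An effect with 80% power on 1 degree of freedom has non-centrality (1.96 + 0.8416)² = 7.85. Spread over 5 degrees of freedom, the same non-centrality gives 55.5% power, a loss of 24.5 points. This agrees with the first row.

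**5. Sensitivity to the borrowed inputs.** With six grades and OR 2.077, putting 30%, 60% or 70% at grade 0 gives losses of 23, 26 and 27 points. With OR 1.5 the loss is 15–20 points.

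**6. Where the comparison reverses.** Both cases use distribution A.

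- Grades 2–5 halved, those patients moved to grade 1, any-complication rate unchanged: chi-square 72%, Mann-Whitney 19%.
- The whole 17.5-point fall taken from grade 1, grades 2–5 unchanged: chi-square 97%, Mann-Whitney 46%.

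**7. Sparse cells.** With 1:1 allocation, a grade needs about 10 patients overall to have an expected count of 5 in each arm. Under A, grade 4 is expected in 119 × (0.03 + 0.015) ≈ 5.4 patients and grade 5 in 119 × (0.02 + 0.01) ≈ 3.6. That puts 4 of 12 cells (33%) below 5. The plan's fallback, Fisher, also ignores order. Its power was not computed here.

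**The case against.** **The power loss rests on borrowed inputs.** This stands. The 50% rate belongs to the ARISCAT-defined composite. Table 4 grades a different set of events: dry cough and dyspnea count as grade 1, grade 2 needs at least two items, and effusion counts only if it leads to thoracentesis. Neither 50% at grade 0 nor the odds ratio of 2.077 is given for the grade.

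**The loss shrinks or reverses in plausible cases.** This also stands. Severe grades may be rare in elective ASA I–III patients, so fewer than six levels may be occupied. If the effect lies at one grade boundary only, chi-square can have much more power than a rank test. A reader might infer that the plan simply forfeits 25 points of power; the documents do not support that.

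**The weight of the outcome.** A reader might take the grade for a key secondary outcome because the abstract lists it first. The article ranks no secondary outcome as key, and Outcome measurements lists the grade after 30-day complications, surgical site infection, and nausea and vomiting.

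**A significant result would still be readable.** Largely right. Categorical variables are to be reported as percentages, so the direction could be seen by eye. The test itself remains non-directional and supplies no estimate. Mann-Whitney alone is also only a test unless an effect measure is reported with it.

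**Test selection may be settled in an analysis plan not shown.** This softens the point but does not remove it: the article names a test for all secondary outcomes and limits the rank test to continuous data.

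**Conclusion.** The mismatch holds: a test for unordered categories is specified for an ordered outcome, and nothing else in the article covers the grade. That conclusion needs no assumed distribution.

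The size is conditional. If the shift is ordered, of the primary outcome's magnitude, with 50% at grade 0 and about 119 analysed per arm, chi-square gives up about 20–25 points against a rank test with six grades occupied, about 15 with four and 6–9 with three. If the effect is not a shift spread across the grades, the ordering of the two tests can reverse.

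This is a worthwhile correction to a secondary analysis. The primary outcome is binary, so its test, the sample size of 252 and the trial's main conclusion are untouched.

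**What to change.** Before unblinding, replace the blanket rule with one sentence for the grade: the severity grade at day 7 and day 30 will be analysed with an ordinal method, either a proportional-odds model reporting the common odds ratio with its 95% CI, or Mann-Whitney U. Show the full grade distribution by arm at both time points, so that an effect confined to one part of the scale can be seen. Keep chi-square and Fisher for the binary outcomes.

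The cost is small: both methods are standard, and Mann-Whitney is already in the plan. There are two downsides. The proportional-odds assumption needs a check, and an ordinal test has less power against patterns that are not an ordered shift.
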